#### Sample size consideration

A previous study showed a nearly 40% reduction of BNP levels in patients with congestive heart failure receiving nocturnal oxygen therapy [12]. Based on our own data of a previous trial (unpublished data) we observed a fourfold increase of BNP (preoperative 129.05 ng/L ± 160.13 to up to 482.49 ng/L ± 538.78) in the postoperative period in relatively healthy patients undergoing moderate- to high-risk open abdominal surgery. We calculated a needed sample size of 254 patients (127 patients per group) to show a 40% reduction of NT-proBNP in patients receiving 80% versus 30% oxygen with a power of 80% at a 0.05 significance level. We will thus include 260 patients (130 patients per group) to compensate for potential drop outs.

### Assignment to intervention

Given an average estimated recruitment rate of 10 patients per month, we anticipate a recruitment period of 25 months. A trained study coordinator will evaluate eligibility and obtain informed consent. All patients will be recruited using the operation schedule the day before surgery. After meeting the eligibility criteria, the inclusion criteria will be checked. Two copies of the signed consent form will be made. One copy remains in the patient chart, and the second one will be given to the patient. On the consent form, participants will be asked if they agree to the use of their data should they choose to withdraw from the trial. Participants will also be asked for permission for the research team to share relevant data with people from the Universities taking part in the research or from regulatory authorities, where relevant. This trial does not involve collecting biological specimens for storage.

On the day of surgery the coordinator will enroll the participants via accessing the web-based system. We will use permutated block randomization using a web-based randomization program (Randomizer, Medical University of Graz, Graz, Austria). Each block has a size of 6 numbers, randomly ordered to the two treatment assignments, of which all investigators were unaware. The web-based randomization program was set up by an investigator not involved in data acquisition. Intraoperative investigators and clinicians will be not blinded to the allocated treatment group. However, an observer strictly blinded to the group assignment will evaluate complications during hospitalization. Subsequently, a blinded investigator will call all patients 30 days after surgery and to evaluate outcomes.

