### Protocol

We will perform standardized monitoring including electrocardiogram (ECG), blood pressure and oxygen saturation (SpO_2_) in all patients after arriving in the operating theater. Shortly before induction of anesthesia, patients will be randomly assigned to one of the two oxygen concentrations. We will administer 100% oxygen in all patients for induction of anesthesia according to clinical standards. We will induce anesthesia using 1–3 μg kg^− 1^ body weight (BW) fentanyl, 2 mg kg^− 1^ (BW) propofol and 0.6 mg kg^− 1^ rocuronium. In addition to standard monitoring, an arterial line will be inserted for direct blood pressure monitoring. A central venous line will be inserted at the discretion of the attending anesthesiologist.

Anesthesia will be maintained with sevoflurane (up to 1.5 minimum alveolar concentration (MAC)) in an oxygen gas carrier according to processed electroencephalogram (EEG)-guided anesthesia. Muscle relaxation will be given when necessary to maintain one to two mechanical twitches in response to supra-maximal stimulation (Train-of-Four stimulation, target < 75%). Temperature will be held at a core temperature over 36 °C using forced-air warming.

We will use esophageal-Doppler-guided (Cardiac Q, Deltex Medical, Chichester, UK) fluid management according to a previously published algorithm [17, 18]. All patients will receive a 2 mL/kg BW baseline infusion of balanced crystalloids. A bolus of 250 mL balanced crystalloids will be administered when the stroke volume decreases by more than 20% as compared to baseline values. In the case of acute bleeding or a systemic inflammatory response during surgery, volume will be administered according to fluid requirements to maintain hemodynamic stability. Blood and blood products will be administered per clinical judgment.

There will be no restrictions or prohibitions of medical care and therapeutics during hospital stay in case of enrollment.

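### One fixed block size of 6, at a single centre with unblinded theatre staff, makes up to a quarter of allocations predictable to anyone who learns the size and tracks assignments

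*Protocol article*

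**What the plan says.** All places are in the protocol article.

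- **Block scheme** (Assignment to intervention): "Each block has a size of 6 numbers, randomly ordered to the two treatment assignments, of which all investigators were unaware". One size is given.
- **Release and set-up** (same section): allocation comes from a "web-based randomization program (Randomizer, Medical University of Graz, Graz, Austria)", and "The web-based randomization program was set up by an investigator not involved in data acquisition".
- **Who sees assignments** (same section): "Intraoperative investigators and clinicians will be not blinded to the allocated treatment group".
- **Who screens and enters** (same section): "A trained study coordinator will evaluate eligibility and obtain informed consent". Then: "On the day of surgery the coordinator will enroll the participants via accessing the web-based system".
- **Timing**: "All patients will be recruited using the operation schedule the day before surgery" (Assignment to intervention), and "Shortly before induction of anesthesia, patients will be randomly assigned to one of the two oxygen concentrations" (Protocol).
- **Setting and size**: one centre (Objectives and design); 260 patients, 130 per group (Sample size consideration); about 10 patients a month (Assignment to intervention).

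**The concern.** Permuted blocks of constant size have a known weakness. Once one arm has used its share of a block, every remaining assignment in that block is fixed. This does little harm when assignments are masked or spread over many sites. Here there is one site, and the intraoperative investigators and clinicians know each assignment as it happens. The role that judges eligibility also performs the entry step, on the day after recruitment. The article does not say that a consented patient must be entered.

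If someone with a say over entry can foresee the next arm, a sicker patient could be held back or entered accordingly. A patient who is never entered is never randomized, so the intention-to-treat rule cannot repair the loss. Blinded outcome assessment does not address it either. The primary outcome is sensitive to patient mix: the planning data give NT-proBNP of 129.05 ± 160.13 ng/L before and 482.49 ± 538.78 ng/L after surgery. The stated primary test is a Mann-Whitney *U* comparison without adjustment for baseline.

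**Working it through.** The article gives no predictability figure to reproduce. The sample-size calculation plays no part in this point.

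**Inputs.** Block size 6 and about 10 patients a month (Assignment to intervention). Equal allocation, hence 3:3 within a block, and N = 260 (Sample size consideration).

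**1. Assignments forced by earlier ones.** A 3:3 block has C(6,3) = 20 equally likely orders. An assignment is forced when one arm already has its three patients.

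| Position in block | 1 | 2 | 3 | 4 | 5 | 6 |
|---|---|---|---|---|---|---|
| Chance of being forced | 0 | 0 | 0 | 10% | 40% | 100% |

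The sum is 0.1 + 0.4 + 1.0 = 1.5 per block, and 1.5/6 = 25%. The general formula for m per arm agrees: 2m/(m + 1) = 6/4 = 1.5.

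Over the trial, 260 = 43 × 6 + 2. The last two patients start a new block and are never forced, so the expected count is 43 × 1.5 = 64.5, about 65 of 260 (24.8%).

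**2. Best-guess rate.** An observer who always guesses the arm with fewer patients so far, and tosses a coin when level, is right m + 2^(2m−1)/C(2m,m) − 1/2 times per block. For m = 3 this is 3 + 32/20 − 0.5 = 4.1, and 4.1/6 = 68.3%, against 50% by chance.

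**3. Can the size be inferred?** This step rests on an assumption: the observer sees every assignment in order from the first patient and considers constant sizes 2, 4, 6, 8 and 10. In simulation, every size but 6 is ruled out after a median of 32 patients, and by patient 80 in 90% of runs. At 10 patients a month, 32 patients is a little over three months of the planned 25.

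**4. Effect of varying the block size.** Here the observer is assumed to know the set of sizes but not each draw (1,000 simulated trials of 260; fixed 6 by enumeration).

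| Block sizes | Known with certainty | Best guess right |
|---|---|---|
| 6 only | 25% | 68.3% |
| 4, 6 | 5.6% | 69% |
| 4, 6, 8 | 2.3% | 68% |
| 6, 8, 10 | 1.5% | 66% |

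The formula in step 2 confirms the last column for 4/6/8: (2.833 + 4.1 + 5.329)/18 = 12.26/18 = 68.1%. Guessing the lagging arm does not require the block size, so varying it removes certainty but leaves the guessing advantage.

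**The case against.** The best case for the plan is that the same section already describes sound safeguards. Allocation is released by a web program, set up by someone outside data acquisition, after recruitment and shortly before induction. The sentence on blocks says investigators were unaware. In-hospital complications and the 30-day call are assessed blind, the primary outcome is a laboratory value, and baseline NT-proBNP will be compared between groups, so gross selective entry would probably show.

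Much of this stands, and it rules out several stronger readings:

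- *Concealment is not secured.* Not supported. Web release after consent protects against an open list. What it does not protect against is inference late in a block.
- *A quarter of allocations were known in advance.* Not supported. This needs knowledge of the size and complete tracking. The article does not say that the coordinator sees or tracks earlier assignments, or that theatre staff decide on entry.
- *The published block size aided prediction.* It could not have. Recruitment ended in December 2019 (Trial status) and the article appeared in May 2020.
- *The sequence is unstratified.* This would be read only from the silence of a condensed article.
- *130 per group is at risk.* Trivial. The worst split with blocks of 6 is 131:129, and both exceed the required 127.

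The objection does not remove the core. It is unclear whether investigators were unaware of the size or only of the order within blocks, and a constant size can in principle be worked out from the sequence. The article itself states the constant size, so this is not a matter of omitted detail.

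**Conclusion.** The point holds as a conditional weakness of design. For an observer who knows or infers the block size and follows every assignment, an average of 25% of allocations (about 65 of 260) are fully determined; for anyone less informed the share is smaller. The stated protection against this is investigators' unawareness of the scheme. Given one site, unblinded theatre staff and one role covering both eligibility and entry, concealment late in a block is weaker than it need be.

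The arithmetic assumes 3:3 blocks run as one sequence; strata, if the full protocol has any, would make tracking harder. A reader might infer that entry was selective or that the primary comparison is biased. The document gives no evidence of either, and no size of bias can be derived from it.

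**What to change.** In Assignment to intervention, replace the constant block of 6 with block sizes varied at random (for example 4, 6 and 8), generated in the same web program, and withhold the sizes from enrolling and intraoperative staff. Add that the program releases the allocation only once the patient has been irrevocably entered. The second part matters as much as the first: varying the size cuts certain predictions to about 2% (0.023 × 260, about 6 patients) but leaves the best-guess rate near 68%.

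The cost is a program setting and a sentence or two. The downside is a possible final imbalance of a few patients: an incomplete last block of 8 can differ by at most 4, so 132:128 at worst, still above 127 per group.

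Because recruitment is complete, what can still be done for this trial is reporting: state who knew the block size and whether the coordinator could see earlier assignments, give the number consented but not randomized, and show baseline NT-proBNP by arm and position in the block.

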### Data collection, management and analysis

Data will be recorded in electronic case report forms (eCRFs) and reviewed by the clinical research associate (CRA) during monitoring visits. The CRA will verify recorded data in the electronic data

capture (EDC) system with the stored source documents. All corrections or changes made to any study data will be appropriately tracked in an audit trial in the EDC system An eCRF will be considered completed when all missing, incorrect, and/or inconsistent data have been accounted for.

For data management we will use Clincase software (Version 2.6.0.34, Quadratek, Berlin, Germany).

All records of subjects, source documents, monitoring visit logs and CRFs will be kept locked in the appropriate study files in our site.

#### Monitoring

The designated monitor will contact and visit the investigator on a regularly basis and will be allowed to have access to all source documents, which are needed to verify the entries in the CRF and eCRF, respectively, and other protocol-related documents. It will be the responsibility of the monitor to inspect the CRFs and eCRFs, respectively, at regular intervals according to the monitoring plan throughout the study, to verify the adherence to the protocol and the completeness, consistency and accuracy of the data being recorded. The monitoring will be performed by [name], Department of Anaesthesia, Intensive Care Medicine and Pain Medicine.

### Access to data

Any data required to support the protocol can be supplied on request.

### Ethics and dissemination

#### Data Safety Monitoring Board

The Data Safety Monitoring Board (DSMB) will be formed by [name], Department of Anaesthesia, Intensive Care Medicine and Pain Medicine, Medical University of Vienna, and [name], Department of Surgery, Medical University of Vienna. The DSMB will evaluate serious adverse events (SAEs) from the trial after 100 enrolled patients. This committee, along with the Local Ethics Committee will have the exclusive authority to stop the study either because the hypothesis has been confirmed or denied, or because the adverse events are overwhelming. Any morbidity potentially related to the study protocol will be reported to the Ethics Committee.

When the data of 100 patients become available the DSMB will evaluate possible overwhelming harmful effects between both study groups and discuss whether to stop the trial early to prevent harm. The DSMB will monitor for an adverse impact of oxygen on SAEs.

The Trial Steering Group and the independent Data Monitoring and Ethics Committee will meet to review conduct throughout the trial period.

#### Adjudication of the trial outcomes

The outcome adjudicator will be blinded to treatment allocation and will adjudicate the following outcomes: death, myocardial infarction, acute heart failure, cardiac arrhythmias and unplanned ICU admission. We will use the decisions of the outcome adjudicator for all statistical analysis of these events. [name] (Department of Anaesthesia, Intensive Care Medicine and Pain Medicine) will chair the Adjudication Committee.

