## Methods/design: data collection, management and analysis

### Objectives and design

We will conduct a single-center, double-blinded, two-arm trial at the Medical University of Vienna. In total, we will randomly assign 260 patients to receive 80% versus 30% inspired oxygen concentration for surgery and for 2 h postoperatively. We will follow the Standard Protocol Items: Recommendations for Interventional Trials (SPIRIT) recommendations for interventional trials (Additional file 1). The study was approved by the Ethics Committee of the Medical University of Vienna on 13 November 2017. This trial was registered at ClinicalTrials.gov on 8 December 2017 (NCT03388957) and at the European Clinical Trial Database (2017–003714-68).

This trial will test the primary hypothesis that supplemental oxygen significantly decreases the maximal postoperative NT-proBNP concentration (assessed within 2 h after surgery, on POD 1 and POD 3) in patients with increased cardiovascular risk factors undergoing moderate- to high-risk abdominal surgery.

Our secondary outcomes are differences in maximum TnT concentration, static oxidation-reduction potential (sORP) and oxidation-reduction potential capacity (cORP), as well as vWF values and the perioperative fluid requirements to reach hemodynamic stability (Table 1).

**Table 1 Tab1:** Outcomes assessment

	Outcomes	Measurements
Primary	Myocardial function	maxNT-proBNP
Secondary	MINS	maxTnT
	Surgical stress	Copeptin
	Redox stress	sORP, cORP
	Hemodynamic	
Exploratory	Cardiac failure	50% increase in NT-proBNP
	Myocardial infarction	ECG change and elevated heart-specific enzymes
	Heart failure requiring intervention	50% NT-proBNP increase and medical treatment
	New onset of cardiac arrhythmias	ECG changes requiring medical treatment and/or electric cardioversion
	Unplanned ICU admission	

c*ORP* oxidation-reduction capacity, *ECG* electrocardiogram, *ICU* intensive care unit, *maxNT-proBNP* maximal *N*-terminal pro-B-type natriuretic peptide, *maxTnT* maximal troponin T, *MINS* Myocardial Injury after Noncardiac Surgery, *sORP* static oxidation-reduction potential

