### Intervention

After endotracheal intubation we will set the inspired oxygen fraction according to randomization. Patients randomly assigned to the 80% oxygen group will receive an inspired oxygen fraction of 0.8 after intubation; those randomly assigned to the 30% oxygen will receive an inspired oxygen fraction of 0.3 in air. Patients will be blinded to group allocation.

We will use 80% versus 30% oxygen concentration to receive the maximum difference between oxygen concentrations without the risk of causing damage, e.g., increased formation of atelectasis [19]. Moreover, almost all studies investigating the effect of supplemental oxygen on, for example, postoperative wound infection used 80% versus 30% inspired oxygen concentration during surgery [5, 6, 20].

Maintaining a minimum SpO_2_ of at least 93% will be attempted. In the case of SpO_2_ < 93% the following interventions to improve oxygenation will be performed: (1) positive end-expiratory pressure (PEEP) will be increased incrementally by 2 cmH_2_O up to maximally 12 cmH_2_O; (2) recruitment maneuver: the inspiratory pressure will be set at 55 cmH_2_O. The PEEP will be set at 12 cmH_2_O and respiratory rate to six breaths/min or higher. Inspiratory pressure will be set to receive a tidal volume of 6 mL/kg ideal BW. The inspiratory ratio will be set (I:E) to 1:1. Inspiratory pressure will be increased until a plateau pressure reaches 40–50 cmH_2_O. After allowing three breaths while maintaining a plateau pressure of 40–50 cmH_2_O, the respiratory rate and inspiratory pressure will be set back to pre-recruitment parameters and (3) if both interventions are not sufficient to increase SpO_2_, then the inspiratory oxygen fraction will be elevated by 0.1 until 93% SpO_2_ is reached.

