#### Follow-up

Patients will be followed up for the primary and secondary outcome within 2 h after surgery, on POD 1, POD 3 and within 3 days before discharge. Laboratory measurements for outcome assessments are shown in Table 1. We will further perform a telephone follow-up on the 30th day after surgery to evaluate cardiac events including acute heart failure, myocardial infarction and new onset of atrial fibrillation (Table 2). All follow-up measurements will be performed by an investigator who will be unaware of the randomized allocation. Acute heart failure will be defined as cardiac failure needing medical intervention including therapy with inotropes and extracorporeal membrane oxygenation. Myocardial infarction will be diagnosed according the fourth definition of myocardial infarction [21]. Atrial fibrillation will be diagnosed according to the management guidelines for atrial fibrillation [22].

**Table 2 Tab2:** Schedule of study events

Timepoints		Study period						
	Enrollment	Intervention			Postoperative period			Close out
	Preoperative visit	Before anesthesia	During surgery	End of surgery for 2 h after surgery	POD 1	POD 3	Hospital discharge	POD telephone follow-up

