#### Data analysis

Randomized groups will be compared for balance in patient characteristics, demographic data, type of surgery, duration of surgery and anesthesia and preoperative baseline laboratory values (including: NT-proBNP, TnT, hemoglobin, hematocrit, leukocytes, thrombocytes, prothrombin time, activated prothrombin time, sodium, potassium, calcium, magnesium, creatinine, albumin, transaminases, C-reactive protein). The primary analysis will be intention to treat so that all randomized patients will be included in all analyses.

The primary outcome, the effect of 80% versus 30% oxygen on postoperative maxNT-proBNP will be compared using a two-sample, two-tailed Mann-Whitney *U* test. If a patient dies before NT-proBNP on POD 3 is measured, the patient’s maxNT-proBNP will be set to the maximum maxNT-proBNP values over all patients. Multiple imputation will be used for missing postoperative measurements.

Our secondary outcomes including Myocardial Injury after Noncardiac Surgery (MINS) (defined as absolute change of high-sensitive TnT of 5 ng/L between 20 to < 65 ng/L) [23], surgical stress, redox stress and perioperative hemodynamic (fluid and vasopressor requirements) will be analyzed using a two-sample, two-tailed Mann-Whitney *U* test. The exploratory outcomes including cardiac failure, myocardial infarction, acute heart failure requiring intervention, new onset of cardiac arrhythmias and unplanned ICU admission will be analyzed using Kaplan-Meier curves assessed with a log-rank test (Table 1).

If hospital discharge occurs before the third POD, the maximum value of the available data will be used for outcome measure.

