### Reporting of serious adverse events (SAE)

Serious adverse events are those which are fatal, life-threatening or fulfill the definition of being clinically important. Efficacy or safety outcomes will not be considered as SAEs, except if, because of the course of severity or any other feature of such events, the investigator, according to their best medical judgment, considers these events as exceptional in this medical condition. All events considered as part of the primary, secondary, or safety events should be reported on the appropriate page(s) in the CRF but not as an SAE, unless considered exceptional in this medical condition. In this trial, the following events (pulmonary failure, cardiac failure, myocardial infarction, acute heart failure, new onset of cardiac arrhythmias, unplanned ICU admission) are considered related to the underlying cardiovascular disease and are not considered as a SAE. These events will not be considered unexpected unless their course, severity or other specific features are such that the investigator, according to their best medical judgment, considers these events as exceptional in the context of the patient. Only unexpected and not previously described SAEs that are believed with a reasonable level of certainty to be associated with the trial medication need to be reported immediately (i.e., within 24 h of knowledge of the event) to the sponsor of the trial, the Medical University of Vienna. For such events, research personal will complete the SAE CRF immediately. Regulatory authorities will be informed in a timely manner according to the applicable regulations.

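### Pulmonary failure is exempt from SAE reporting without being an outcome, and death is adjudicated for analysis without an outcome row or a between-arm analysis

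*Protocol article*

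**What the plan says.** Five parts of the protocol article list events.

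- **Adjudication of the trial outcomes.** The blinded adjudicator "will adjudicate the following outcomes: death, myocardial infarction, acute heart failure, cardiac arrhythmias and unplanned ICU admission". The section goes on: "We will use the decisions of the outcome adjudicator for all statistical analysis of these events".
- **Objectives and design, Table 1.** The exploratory rows are cardiac failure, myocardial infarction, heart failure requiring intervention, new arrhythmias and, last, "Unplanned ICU admission". There is no row for death or for any pulmonary event.
- **Data analysis.** Kaplan-Meier curves with a log-rank test are named for the same five: "The exploratory outcomes including cardiac failure, myocardial infarction, acute heart failure requiring intervention, new onset of cardiac arrhythmias and unplanned ICU admission". Death appears in this section only as a scoring rule for the primary outcome: "If a patient dies before NT-proBNP on POD 3 is measured", the patient receives the largest maxNT-proBNP seen in any patient.
- **Follow-up.** The day-30 call is "to evaluate cardiac events including acute heart failure, myocardial infarction and new onset of atrial fibrillation".
- **Reporting of serious adverse events.** Fatal events are SAEs. Six events are set aside as related to the underlying cardiovascular disease and not counted as SAEs: "pulmonary failure, cardiac failure, myocardial infarction, acute heart failure, new onset of cardiac arrhythmias, unplanned ICU admission".

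The Data Safety Monitoring Board section gives the DSMB one stated review, when data on 100 patients are available, and describes its monitoring in terms of SAEs. The Intervention section says 80% versus 30% was chosen to give the widest contrast "without the risk of causing damage, e.g., increased formation of atelectasis".

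**The concern.** Exempting an event from SAE reporting is reasonable when the trial captures and analyses it as an outcome instead. For five of the six exempt events that holds. For pulmonary failure it does not: the exemption removes one route and nothing named replaces it. The stated ground is cardiovascular disease, although the treatment is inspired oxygen and the protocol's own example of oxygen damage is in the lung.

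Death shows the opposite mismatch. It is adjudicated so that it can be analysed, but no analysis of it is listed. The Discussion supports the trial partly by citing a subanalysis with a 30% reduction, at 80% oxygen, in a composite that includes mortality.

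What is at stake is the balance of the final report. The primary outcome is a biomarker. A favourable NT-proBNP result could be published with no planned account by arm of lung failure or of deaths after POD 3.

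**Working it through.** No stated figure is in dispute, so the check is a side-by-side reading of the lists, followed by an illustration of what a comparison could show.

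**1. The lists set side by side**

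| Event | SAE-exempt | Table 1 row | Log-rank analysis | Adjudicated |
|---|---|---|---|---|
| Pulmonary failure | yes | no | no | no |
| Cardiac failure | yes | yes | yes | not named |
| Myocardial infarction | yes | yes | yes | yes |
| Acute heart failure (needing intervention) | yes | yes | yes | yes |
| New arrhythmias | yes | yes | yes | yes |
| Unplanned ICU admission | yes | yes | yes | yes |
| Death | no | no | no | yes |

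Of the six exempt events, five have a row and an analysis; pulmonary failure has neither. Of the five adjudicated events, four have a row and an analysis; death has neither. The exemption list is the only place in the article where pulmonary failure is mentioned, and no definition is given.

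**2. What remains for each event**

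- *Pulmonary failure.* As a non-SAE it is outside the DSMB's stated SAE monitoring, unless the investigator judges a case exceptional. It can still be recorded in the general adverse-event row of Table 2 or as a safety event on a CRF page. Neither names it or leads to a stated comparison.
- *Death.* A death before the POD 3 sample takes the worst value in the Mann-Whitney test of the primary outcome. A later death changes nothing in that test. Fatal events are SAEs, so the DSMB can see them at its look at 100 patients; the remaining 260 − 100 = 160 patients come after that look.

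**3. What a comparison could show**

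Inputs: 130 patients per group (Sample size consideration) and two-sided 0.05. The documents give no rate for either event, so control-arm risks p₁ of 1%, 2%, 3% and 5% are assumptions, and p₂ is the risk in the other arm. With p̄ the mean of p₁ and p₂,

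power = Φ{ [(p₂ − p₁)√n − 1.96√(2p̄(1 − p̄))] / √(p₁(1 − p₁) + p₂(1 − p₂)) }.

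For 2% versus 4%: (0.02 × √130 − 1.96 × √0.0582) / √0.0580 = (0.228 − 0.473) / 0.241 = −1.02, so power is about 0.155.

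| Assumed control risk | Expected control events (130 × p₁) | Power for a doubling | Smallest risk in the other arm detectable at 80% power |
|---|---|---|---|
| 1% | 1.3 | 10% | 8.3% |
| 2% | 2.6 | 16% | 10.4% |
| 3% | 3.9 | 21% | 12.2% |
| 5% | 6.5 | 33% | 15.5% |

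Counts by arm with confidence intervals are what this trial can offer for either event. A formal test would be uninformative.

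**The case against.** A reader might infer that neither harm is ever compared between arms and that pulmonary failure is not collected at all. The text does not support that.

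- Early deaths enter the primary test at the worst value, so an excess of them in the 80% arm would count against that arm.
- Fatal events are SAEs, and the DSMB is to consider harmful effects between the two groups.
- Table 2 marks adverse events from surgery through to the telephone follow-up. The SAE section sends safety events to CRF pages. A blinded observer evaluates complications during the hospital stay. Severe lung failure may also surface as an unplanned ICU admission.
- The day-30 list is open-ended and cannot be read as excluding death.
- Missing adjudication does not by itself single out pulmonary failure, because cardiac failure is not named for adjudication either.
- Atelectasis is cited to explain the choice of concentrations, not as a forecast of pulmonary failure.
- The article condenses a fuller protocol, and a SAP may tabulate deaths. How deaths are handled in the Kaplan-Meier curves is likewise a matter for a SAP and is not part of this point.

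All of this stands, and it narrows the point. It does not remove the mismatch, which lies in text the article states. Possible capture as an unspecified adverse event is not a named comparison. The worst-value rule stops at the POD 3 sample, and one early DSMB look is a stopping review. Low power is a reason to report counts rather than a test, not a reason to omit them.

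**Conclusion.** The point holds as an inconsistency between the protocol's own lists. Pulmonary failure is exempt from SAE reporting without being a listed, adjudicated or analysed outcome: one of six exempt events. Death is adjudicated for analysis without an outcome row or a between-arm analysis: one of five adjudicated events. The pulmonary half is the stronger, because the exemption also takes the event out of the DSMB's stated SAE review.

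The list comparison rests on no assumption beyond matching acute heart failure to the Table 1 row on heart failure requiring intervention. The power figures rest wholly on assumed risks of 1% to 5% and show only that any comparison is descriptive. The primary analysis and the sample size are unaffected. The documents do not show that either harm differs between arms or goes unrecorded.

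**What to change.** Reconcile Table 1, Data analysis, Adjudication of the trial outcomes and Reporting of serious adverse events:

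1. Either make pulmonary failure a safety outcome, with one definition fixed before unblinding and blinded adjudication, or take it off the list of SAE-exempt events.
2. List all-cause death to day 30 as a safety outcome. State at the same time that fatal events remain SAEs, because the SAE section generally exempts safety outcomes and could otherwise be read as removing them.
3. Report counts of both events by arm with confidence intervals, labelled descriptive.

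Trial status says recruitment was completed in December 2019, so new CRF pages or call questions are no longer feasible. The work has to use records already collected: adverse-event entries, medical records and the day-30 contacts. The cost is a few lines of text and minor extra work for the existing adjudicator. The limits are that pulmonary failure, classified retrospectively, will be only as complete as those records, and that the comparison will be imprecise at 130 per arm.
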